## Abstract

**Background:**

Poor mental health among adolescent girls during pregnancy and the year after birth (the perinatal period) has been found to have a significant detrimental effect on girls and their children. The Innovative approaches to adolescent perinatal wellbeing (INSPIRE) project co-designed an intervention (Thriving Mamas) to improve adolescent perinatal mental health in Kenya and Mozambique. The aim of the current study is to pilot test the co-designed intervention to understand how it can be adapted for further testing or scale-up.

**Methods:**

A mixed-method, pilot cluster-randomised, effectiveness-implementation Hybrid Type II trial will be conducted among 80 adolescent girls (aged 15–19 years) attending health facilities in Kenya and Mozambique. Girls attending health facilities randomised to the intervention arm will be recruited to receive the intervention in addition to usual care. Girls attending control arm facilities will receive usual care only. Implementation data on feasibility, acceptability, appropriateness, and fidelity of intervention training and delivery will be collected from providers and adolescents. Additional data on provider knowledge, attitudes, and competency will be collected pre- and post-training. Adolescent girls will provide assessments of depression, anxiety, quality of life, social support, parenting competency, and health behaviours before, during, and after delivery of the intervention. At the end of the study, qualitative interviews will be conducted to collect further data on perceptions of the intervention, its implementation, and its impact. Implementation data will be analysed to determine its potential for delivery and success within each context. Individual outcome data analyses will be reported to gain a better understanding of the initial impact of the intervention.

**Discussion:**

The Thriving Mamas intervention addresses the challenges to maintaining positive mental health during the perinatal period. It was co-designed with adolescents and their communities to address local priorities and needs. The results of this study will provide information on its potential for sustainable implementation as well as initial data on its impact on mental health, parenting, and health behaviour outcomes. These results will inform the further refinement of the intervention and implementation strategies as well as the design of a full trial to test their effectiveness.

**Trial registration:**

Ethical approval for this feasibility study has been obtained in Kenya (Aga Khan University Institutional Scientific and Ethics Review Committee, ref: 2023/ISERC-23 (v2)), Mozambique ( Tete Inter-Institutional Health Bioethics Committee, ref: 24/CIBST/23), and the UK (Psychiatry, Nursing and Midwifery Research Ethics Committee, King’s College London, ref: HR/DP-22/23–37,125). It was registered at Clinicaltrials.gov (NCT06040359) on September 15, 2023 (https://clinicaltrials.gov/study/NCT06040359?intr=Thriving%20mamas&rank=1 ), prior to the beginning of the study.

## Background

Mental wellbeing during the perinatal period (i.e. pregnancy and the year after childbirth) is critical due to its important influence on the physical and mental health and social outcomes of mothers and their children. Pregnant adolescents in low- and middle-income countries (LMICs) often experience a variety of adverse events (e.g. family conflict, poor social support, poor self-esteem, gender discrimination, exclusion from education, and poverty) which increase their risk for mental health problems [1]. In Kenya and Mozambique, an estimated 1 in 3 adolescents experience a mental disorder during pregnancy and the year after birth [2, 3]. Despite a clear need for support, no adolescent maternal mental health prevention interventions have yet been evaluated in sub-Saharan Africa, where the majority of the world’s adolescent mothers live [4].

The Innovative approaches to adolescent perinatal wellbeing (INSPIRE) project aims to address the implementation difficulties of mental health interventions through a blend of human-centred design [5], systems thinking [6, 7], and implementation science [8]. From October 2021 to February 2023, the research team partnered with key stakeholders (i.e. adolescent girls, their families, service providers, and community representatives) to identify priority challenges to adolescent perinatal mental health and develop an intervention to address them [9]. This protocol provides detail of the pilot evaluation of the intervention. The results will inform the further refinement of the intervention and implementation strategies as well as the design of a full trial to test their effectiveness. Through these methods, it is hoped that the resulting intervention will align with the needs, goals, and priorities of those directly and indirectly involved in its success and have increased chances of integration into existing health and community systems.

### Aim and objectives

The aim of the pilot is to refine the Thriving Mamas programme to improve its implementation and impact on the mental health and wellbeing of pregnant adolescent girls and new mothers aged 15–19 years living in Kenya and Mozambique. To achieve this goal, the study has five objectives:Evaluate and understand how local contexts influence stakeholder perceptions of the acceptability, appropriateness, and feasibility of the intervention and its implementation strategies.Explore the impact of the intervention on adolescent mother’s mental health, quality of life, social support, parenting, and health behaviour outcomes.Compare implementation and clinical outcomes in Kenya and Mozambique.Estimate the cost of delivering the intervention.Refine the training materials, intervention content, and procedures for implementation.

## Methods

### Study design

An effectiveness-implementation Hybrid Type II pilot cluster-randomised control trial to concurrently assess and adapt intervention content and delivery will be carried out to address the study research questions and objectives over 12 months. Adolescent girls (aged 15–19 years) will be recruited from health and community settings in which participants randomised to receive the intervention or act as a control. A variety of information, including feasibility, acceptability, appropriateness, fidelity, health and wellbeing, service utilisation, and family planning, will be collected using both quantitative and qualitative methods before, during, and after the intervention. This feedback will be used to further refine the provider training, intervention, and implementation strategies.

### Setting

Research will take place in health and community settings with high rates of adolescent pregnancy in Kilifi County, Kenya, and Tete Province, Mozambique (see Fig. 1). Kilifi County is located in south-west Kenya with a population of approximately 1,453,787 [10]. There are approximately 5,000 births annually.

**Fig. 1 Fig1:**
[figure not shown]
Location of Tete Province, Mozambique (right), and Kilifi County, Kenya (left)

Approximately half of these births are to women under 20 years old [11]. The research will be carried out in two sub-counties of Kilifi, Kaloleni and Rabai, which represent urban and peri-urban settings, respectively. Tete province is located in north-west Mozambique. It has a population of approximately of about 2,648,941 [12]. The estimated adolescent (aged 15–19 years) fertility rate in the province is 198.4 births per 1,000 [12, 13]. In Mozambique, the project will be conducted in Moatize City, the district capital, and Cateme, a rural area approximately 40 km from Moatize City within Tete Province.

### Participants and sampling method

The sample size for the pilot has been selected on the grounds of feasibility of recruitment and retention of participants in both study arms and was informed by local partners and stakeholders. This study aims to enrol 80 adolescent girls and 32 mentor mothers, with a loss to follow-up of 33% for both cadres of study participants. This will enable estimation of the loss of follow-up rate with a 95% CI of ± 17% for mentor mothers and ± 11% for adolescent girls [14, 15]. This, in turn, will provide us with essential information required to calculate the sample size for the main trial.

We also anticipate that our sample size will provide us with insight into whether the intervention is acceptable, appropriate, feasible, and delivered with high fidelity. If our findings suggest otherwise, this will indicate that further work is needed to adapt the intervention and selected implementation strategies, prior to implementation.

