#### Mentor mothers

Up to 16 women will be recruited in each country (total of 32 women across the project) to be trained to deliver the intervention (see Fig. 2). The following inclusion criteria will be used: (a) aged 20 years or older; (b) female; (c) experience of pregnancy and/or parenting; and (d) live within the study site. Women will be excluded from participating if they are unable to attend training or deliver the intervention sessions. Following training, eight women in Mozambique and four women in Kenya will be selected to provide the intervention within the pilot study. Selection will be based on knowledge and attitude scores obtained after training.

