#### Adolescent girls

Up to 40 adolescent girls will be recruited in each country (*n* = 80), through participating community services and health facilities. In Kenya, adolescents will be recruited from local dispensaries. In Mozambique, adolescents will be recruited from primary health centres. The following inclusion criteria will be used: (a) up to 28 weeks pregnant; and (b) aged 15–19 years. They will be excluded from the study if they are unable to provide informed consent or are unable to participate in the intervention, due to existing health conditions.

Adolescent girls who meet the study inclusion criteria will be given information about the study by health facility staff. Those interested in participating will be introduced to a member of the research team, who will provide them with an information sheet and consent form. Where an adolescent is aged 15–17 years, the research team also will discuss the information with their guardian during the same visit, if the guardian is in attendance. If the guardian is not present, a member of the research team will discuss the information sheet with the minor. If she indicates further interest in participating, we will explain that we also require guardian consent due to her age. Following introduction to their guardian, the study will be introduced using the information sheet and consent requested. In this situation, the minor will be required to provide their assent following guardian consent.

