### Randomisation

Allocation to the intervention or control group will be carried out by randomisation of health facilities (clusters). This will ensure the inclusion of an urban and peri-urban site in both the intervention and control groups (i.e. stratification). In both countries, clusters will be geographically separated to reduce the potential for contamination.

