### Feasibility criteria for progression to full trial

The primary objective of this study is to evaluate the feasibility and acceptability of the intervention, its implementation, and trial procedures for a subsequent large-scale evaluation. Overall feasibility and acceptability criteria for progression to a full trial have been informed by Mellor et al.’s [44] trial progression recommendations and retention criteria used in previous mental health research conducted in LMICs [45]. These consist of a mixture of qualitative and quantitative criteria:Identification of qualitative themes reporting that both adolescents and mentor mothers perceive the intervention and mentor training as being acceptable, feasible, and appropriate.Retention of at least 67% (i.e. 33% loss to follow-up) of adolescents and mentor mothers through endline assessments.Fewer than 15% missing items on outcome measures across all assessments.Presence of adverse events among fewer than 10% of participants.Identification of serious adverse events related to intervention delivery.

In domains where criteria are met, we will retain the procedure for the full trial. In domains where criteria are not met, we will modify procedures for the full trial guided by data collected during interviews. The presence of any adverse events and/or serious adverse events will be addressed by the research team to identify alternative strategies for the full trial and Data Safety Monitoring Committee. The number of feasibility, acceptability, and fidelity criteria that are not met will determine the extent of intervention and trial design modification.

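### The ±17% precision for mentor-mother loss to follow-up rests on the 32 women trained, but the endline retention criterion can be measured on only about 12; the ±11% for girls is a best case without clustering

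*Protocol article*

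**What the plan says.** Under Participants and sampling method, the protocol article sets enrolment: "This study aims to enrol 80 adolescent girls and 32 mentor mothers", "with a loss to follow-up of 33% for both cadres of study participants". It says this will allow the loss rate to be estimated with a "95% CI of ± 17% for mentor mothers and ± 11% for adolescent girls", and that the result will feed the sample size calculation for the main trial. The same paragraph says the size itself was chosen on feasibility grounds.

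The Mentor mothers subsection describes two stages. First: "Up to 16 women will be recruited in each country (total of 32 women across the project) to be trained to deliver the intervention". Then, after training, "eight women in Mozambique and four women in Kenya will be selected to provide the intervention within the pilot study", with selection based on post-training knowledge and attitude scores.

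The progression criteria include: "Retention of at least 67% (i.e. 33% loss to follow-up) of adolescents and mentor mothers through endline assessments".

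Table 1 gives mentor mothers two sets of measures. The training measures fall before and after training. The intervention content and delivery measures include acceptability, feasibility, appropriateness, cost and an interview after the intervention.

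For girls, the article says "Up to 40 adolescent girls will be recruited in each country". The Randomisation section allocates health facilities, not individuals. The Quantitative analysis section adjusts PHQ-9 and GAD-7 for clustering and describes the number of clusters as small. It gives no facility count, intracluster correlation (ICC) or design effect.

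**The concern.** A precision statement is useful only if its denominator and time point match the quantity to be estimated. Here the planning figure counts everyone trained, while the criterion it appears to support runs to endline, after 20 of the 32 women have been set aside by design. The article does not say which group the 67% applies to. A reader could therefore believe that mentor-mother retention at endline will be known to within 17 points, when the women who can supply it number about 12.

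For girls, the figure treats 80 participants as independent although they are recruited through randomised facilities, and drop-out may be correlated within a facility.

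These half-widths are the only quantitative support offered for the sample size. They are tied to a numeric progression criterion and to the drop-out assumption for the main trial.

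**Working it through.** **Inputs from the article.** Loss 33%; 32 mentor mothers trained; 8 + 4 = 12 selected to deliver; 80 girls; two-sided 95% interval; retention criterion 67% at endline.

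**Step 1: reproduce the stated figures.** The Wald half-width is 1.96 × √[p(1 − p)/n] with p = 0.33.

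- n = 32: 1.96 × √(0.2211/32) = 16.3 points.
- n = 80: 1.96 × √(0.2211/80) = 10.3 points.

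Exact (Clopper-Pearson) half-widths come closer to the published values:

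- Mentor mothers: 16.9 for 10/32 and 17.3 for 11/32.
- Girls: 10.7 for 26/80 and 10.8 for 27/80.

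These round to 17 and 11. A Wald interval at p = 0.5 also gives 17.3 and 11.0. By any of these routes the denominators are 32 and 80, with no allowance for clustering.

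**Step 2: mentor mothers through endline.** With n = 12:

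- Wald at 33%: 1.96 × √(0.2211/12) = 26.6 points.
- Exact CI for 4/12: 9.9% to 65.1%, half-width 27.6 points.
- Wilson for 4/12: 13.8% to 60.9%, half-width 23.6 points.

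All three are well above 17.

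If 32 is kept as the denominator and only the women who deliver reach endline, 32 − 12 = 20 women (62.5%) count as lost. Retention can then be at most 12/32 = 37.5%, which does not fit the planned 33% loss.

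The threshold is also awkward at this size. 8/12 = 66.7% falls just under 67%, so 9/12 = 75% is needed, and one woman decides the outcome.

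**Step 3: girls with clustering.** The half-width is c × √[0.2211 × DE/80], where DE = 1 + (m − 1) × ICC, m is the number of girls per facility, and c is 1.96 (z) or the t quantile on (facilities − 1) degrees of freedom. The facility counts and ICCs below are assumptions, not figures from the article.

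| Assumed facilities × girls | Method | ICC 0.01 | ICC 0.02 | ICC 0.05 | ICC 0.10 |
|---|---|---|---|---|---|
| 8 × 10 | z | ±10.8 | ±11.2 | ±12.4 | ±14.2 |
| 8 × 10 | t, 7 df | ±13.0 | ±13.5 | ±15.0 | ±17.1 |
| 4 × 20 | z | ±11.2 | ±12.1 | ±14.4 | ±17.6 |
| 12 × 6.7 | z | ±10.6 | ±10.9 | ±11.7 | ±12.9 |

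On the z scale, an ICC of about 0.01 leaves the figure near ±11. It moves clearly away at an ICC of about 0.05 with 8 facilities, and sooner with 4. Both enrolment numbers are also maxima (up to 16 women and up to 40 girls per country), so smaller recruitment would widen every interval.

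**The case against.** The strongest reply is that nothing is miscalculated. The half-widths are right for the enrolled numbers, and all 32 mentor mothers have scheduled assessments before and after training. If loss to follow-up means loss over training, ±17% on 32 is coherent. That stands as arithmetic, but it does not rescue the criterion: the progression section names endline, so on this reading the planning figure and the criterion measure different things, and the article does not say so.

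A reader might go further and infer that the mentor-mother criterion is bound to fail at 37.5%. The documents do not support that. Women whom the team does not select are not lost in the ordinary sense, and the criterion does not say that all 32 form its denominator. The 37.5% shows only what follows if they are counted that way. The pilot flow diagram, which is not available here, may show who is followed to endline and how many facilities take part.

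A reader might also infer that ±11% for girls is definitely too narrow. That too goes beyond the documents, because neither the ICC for drop-out nor the facility count is given. The printed ±11 is slightly wider than the Wald 10.3, enough to cover a design effect of (11/10.3)² = 1.14. What stands is that the figure makes no stated allowance for clustering in a facility-randomised design.

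Finally, the sample size was set on feasibility, the pilot is descriptive, and an unmet criterion leads to modified procedures rather than a stop. This limits the seriousness of the point.

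**Conclusion.** The concern holds in a limited form. The published half-widths are correct for simple random samples of 32 and 80. The ±17% does not apply to mentor-mother retention through endline, where the usable denominator is 12 and the half-width is about ±27 points (Wilson about ±24). This rests on reading endline as the post-intervention assessment and on only the delivering women contributing to it. Table 1 and the selection step point that way, and no section describes endline follow-up of the other 20.

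The girls' ±11% is a best case. Its shortfall is conditional: negligible on the z scale at an ICC near 0.01, and several points at 0.05 to 0.10 or with few facilities.

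The point merits correction but is not critical. It affects how a progression criterion and a planning figure are read; it does not affect a treatment comparison or the number recruited.

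**What to change.** 1. Report mentor-mother retention in two parts: through training (denominator 32, post-training assessment, ±17%) and through delivery to endline (denominator 12, about ±27%).
2. State that the 67% criterion applies to the 12, and note that 8/12 = 66.7% falls just under it, so the team can decide in advance whether 67% or two-thirds is meant.
3. Present the girls' precision as a range from a single method, using the actual number of facilities and a stated ICC range. If there are 8 facilities of 10 and the ICC is 0.02 to 0.10, that is ±11.2 to ±14.2 with z, or ±13.5 to ±17.1 with t on 7 df. The lower end of one method should not be joined to the upper end of the other.
4. Compute the observed interval for girls' loss to follow-up allowing for clustering, with a cluster-robust or cluster-level method.

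The cost is a few restated figures and one denominator definition. The figures become less favourable; no extra participants are needed.

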#### Mentor mothers

Up to 16 women will be recruited in each country (total of 32 women across the project) to be trained to deliver the intervention (see Fig. 2). The following inclusion criteria will be used: (a) aged 20 years or older; (b) female; (c) experience of pregnancy and/or parenting; and (d) live within the study site. Women will be excluded from participating if they are unable to attend training or deliver the intervention sessions. Following training, eight women in Mozambique and four women in Kenya will be selected to provide the intervention within the pilot study. Selection will be based on knowledge and attitude scores obtained after training.

**Fig. 2 Fig2:**
[figure not shown]
Pilot flow diagram

#### Adolescent girls

Up to 40 adolescent girls will be recruited in each country (*n* = 80), through participating community services and health facilities. In Kenya, adolescents will be recruited from local dispensaries. In Mozambique, adolescents will be recruited from primary health centres. The following inclusion criteria will be used: (a) up to 28 weeks pregnant; and (b) aged 15–19 years. They will be excluded from the study if they are unable to provide informed consent or are unable to participate in the intervention, due to existing health conditions.

Adolescent girls who meet the study inclusion criteria will be given information about the study by health facility staff. Those interested in participating will be introduced to a member of the research team, who will provide them with an information sheet and consent form. Where an adolescent is aged 15–17 years, the research team also will discuss the information with their guardian during the same visit, if the guardian is in attendance. If the guardian is not present, a member of the research team will discuss the information sheet with the minor. If she indicates further interest in participating, we will explain that we also require guardian consent due to her age. Following introduction to their guardian, the study will be introduced using the information sheet and consent requested. In this situation, the minor will be required to provide their assent following guardian consent.

#### Friends/family members

Each girl randomised to receive the intervention will be given the opportunity to invite one trusted friend or family member to specific intervention sessions (*n* = 40; see description of intervention arm for details of sessions). The following inclusion criteria will be used: (a) identified by an adolescent or young woman participating in the study; (b) participation agreed by other participating girls; and (c) aged 18 years or older.

